| 1. What health system do you use for your warfarin?                                                 | -Brigham and Women's Hospital
-Loma Linda VAMC
-University of Michigan
-University of Utah                                                                                                                   |                                                                                                                                                                                             |
| 2. What is your study ID?                                                                           | -Patient enters assigned study ID number                                                                                                                                                                              |                                                                                                                                                                                             |
| 3. What is your goal INR range?                                                                     | -2.0-3.0
-2.5-3.5                                                                                                                                                                                                  |                                                                                                                                                                                             |
| 4. Date of INR being reported?                                                                      | -Patient enters date INR performed                                                                                                                                                                                    |                                                                                                                                                                                             |
| 5. Value of INR being reported?                                                                     | -Patient enters INR value                                                                                                                                                                                             | If INR is 5.0 or higher, patient instructed to contact their anticoagulation provider                                                                                                       |
| 6. Based on your INR value, do you plan on adjusting your weekly warfarin dose?                     | -Yes
-No                                                                                                                                                                                                           | If "No" survey skips to question 20                                                                                                                                                         |
| 7. In response to this INR, who ultimately decided the new warfarin dose you will take?             | -I did
-Someone else/healthcare provider
-Other                                                                                                                                                                 | If "I did", question 8 is asked; otherwise, survey skips to question 9                                                                                                                      |
| 8. How did you decide which warfarin dose to take?                                                  | -My warfarin website tool
-My own decision
-Other                                                                                                                                                               |                                                                                                                                                                                             |
| 9. Over the past week what tablet strength of warfarin did you use?                                 | -1 mg (pink)
-2 mg (lavender)
-2.5 mg (green)
-3 mg (tan)
-4 mg (blue)
-5 mg (peach)
-6 mg (teal)
-7.5 mg (yellow)
-10 mg (white)
-I used different tablet strengths (more than one color) |                                                                                                                                                                                             |
| 10. Over the PAST week, how many tablets did you actually take each day (enter 0 for missed doses)? | -Patient fills in a grid with the number of tablets taken each day                                                                                                                                                    | Dates for the grid will auto populate based on the INR date entered for question 4
Total milligrams taken over the previous week automatically calculate from values entered in the grid |
| 11. Since your last INR, which of the following changes have occurred?                              | -Bleeding symptoms
-Clotting symptoms
-New or worsening illness                                                                                                                                                 | If "Bleeding symptoms" question 12 is asked                                                                                                                                                 |

|                                                                         |                                                                                                                                                                                                                                                                                                                                                                                                                                      |                                                                                                                                                                                                                                                                                     |
|-------------------------------------------------------------------------|--------------------------------------------------------------------------------------------------------------------------------------------------------------------------------------------------------------------------------------------------------------------------------------------------------------------------------------------------------------------------------------------------------------------------------------|-------------------------------------------------------------------------------------------------------------------------------------------------------------------------------------------------------------------------------------------------------------------------------------|
|                                                                         | 
 
-Changes in medications
 
-Changes in diet/vitamin K intake
 
-None
 
                                                                                                                                                                                                                                                                                                  | 
If “Clotting symptoms” question 13 is asked
 
If “New or worsening illness” question 14 is asked
 
If “Changes in medications” question 15 is asked
 
If “Changes in diet/vitamin K intake” question 16 is asked
 
If “None” survey skips to question 18
 |
| 12. What bleeding symptoms (select all that apply)?                     | 
 
-Nosebleed
 
-Unusual bruising (i.e., more severe or more frequent than usual)
 
-Heavy menstrual bleeding
 
-Blood in urine (red or pink)
 
-Blood in stool (bright red or black)
 
-Coughing up blood
 
-Throwing up blood
 
-Stroke symptoms such as facial drooping, arm weakness, and/or speech difficulties
 
-Other
 
 |                                                                                                                                                                                                                                                                                     |
| 13. What clotting symptoms (select all that apply)?                     | 
 
-New pain, redness, or swelling of legs or arms
 
-Chest pain (i.e., more severe or frequent than usual)
 
-Shortness of breath (i.e., more severe or frequent than usual)
 
-Stroke symptoms such as facial drooping, arm weakness, and/or speech difficulties
 
-Other
 
                                                                               |                                                                                                                                                                                                                                                                                     |
| 14. What new or worsening illness symptoms (select all that apply)      | 
 
-Fever or infection
 
-Vomiting (i.e., more severe or frequent than usual)
 
-Diarrhea (i.e., more severe or frequent than usual)
 
-Visit to urgent care
 
-Visit to emergency room
 
-Admitted to hospital
 
-Other
 
                                                                                                                    |                                                                                                                                                                                                                                                                                     |
| 15. What changes in medications (prescription, over the counter, and/or | 
 
-Started new medication(s)
 
-Stopped medication(s)
 
-Changed dose of medication(s)
 
                                                                                                                                                                                                                                                                                 | Patients asked to provide details of any changes                                                                                                                                                                                                                                    |

|                                                                                                                                                 |                                                                          |                                                                                                          |
|-------------------------------------------------------------------------------------------------------------------------------------------------|--------------------------------------------------------------------------|----------------------------------------------------------------------------------------------------------|
| supplements) (select all that apply)?                                                                                                           | -Other                                                                   |                                                                                                          |
| 16. What changes in diet/vitamin K intake (e.g., green leafy vegetables, vegetable smoothies, nutrition, or vitamin supplements with vitamin K) | -INCREASED vitamin K intake
-DECREASED vitamin K intake
-Other     |                                                                                                          |
| 17. Did you contact your anticoagulation management service provider regarding these symptoms?                                                  | -Yes
-No                                                              |                                                                                                          |
| 18. Did you already take your warfarin dose for today before checking your INR?                                                                 | -Yes
-No                                                              | Used to auto-populate dates of the grid for question 19                                                  |
| 19. Over the NEXT week, how many tablets do you plan on taking each day?                                                                        | -Patient fills in a grid with the planned number of tablets for each day | Total milligrams to be taken over the next week automatically calculated from values entered in the grid |
| 20. When do you plan on rechecking your next INR?                                                                                               | -Patient enters date of next INR                                         |                                                                                                          |
| 21. Is there anything else you wanted to tell us about today's INR?                                                                             | -Text box for patient comments                                           |                                                                                                          |

INR-international normalized ratio; PSM-patient self-management; VAMC-Veterans Administration Medical Center; ID-identification

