## Participant clinical decision support tools

Participant clinical decision tools for the PSM implementation toolkit will consist of an online dosing tool ("My Warfarin") and a manual dosing method ("DIY dosing"). Participants or their caregivers will also be allowed to make warfarin dosing decisions based on their own

experience without using formal clinical decision support tools if desired. Participants will be instructed to contact their anticoagulation clinician in high-risk situations (e.g., INR <1.5 or >5.0, any bleeding or thromboembolic symptoms, prior to scheduled invasive procedures) or if they want to consult with a clinician for any reason.

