#### PSM implementation phase

Prior to initiating PSM, consenting participants will complete an online survey hosted in REDCap containing the following: 1) the anticoagulation knowledge tool (AKT), a validated 28-item instrument that assesses participants' anticoagulation knowledge; 2) the anti-clot treatment scale (ACTS), a 15-item participant-reported instrument assessing satisfaction with anticoagulant treatment that includes a 12-item Burdens scale and a 3-item Benefits scale; and 3) the Short Form 36 questionnaire (SF-36), a validated instrument used to estimate health-related quality of life.

Participants will complete the previously described interactive online educational module in preparation for initiating PSM. Clinician study team members at each site will use the combination of each participant's PSM knowledge assessment score, comfort level with PSM, and their subjective assessment of the participant's likelihood of success with PSM to determine if they should progress to the "spotters ready" phase where clinicians will provide feedback on the participant's warfarin dosing plans as needed. The "spotters ready" phase will end and the formal PSM phase begin once participants express feeling comfortable starting PSM on their own.

During the 6-month PSM phase, participants will be asked to check INRs every 1 to 2 weeks when INRs are in range and weekly when INR are out of range. Participants will be asked to use clinical decision support tools from the implementation toolkit (My Warfarin, DIY) or use their own experience to make independent warfarin dosing decisions. Participants will be asked to contact clinicians in high-risk situations as previously described or when additional advice is desired.

During the PSM phase, participants will self-report INR results, warfarin dosing decisions, the method used to arrive at dosing decision (i.e., My Warfarin, DIY, or using their own judgement), factors potentially impacting INR response (i.e., changes in other medications, diet, and/or health status), and bleeding/ thromboembolic complications using the previously described online data collection form hosted in REDCap.

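### In the per-INR survey, answering No to a planned dose change skips every symptom question, so symptoms at those INRs may not reach site review

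*Protocol*

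**What the plan says.** **What the survey is for.** Under *Approaches for documenting PSM activities in the EHR*, participants report INRs, dosing decisions, influencing factors and bleeding or thromboembolic events through the REDCap survey. A summary is emailed to the site team so that it can review and intervene where harm is possible. *PSM implementation phase* repeats the self-report of complications. Figure 1 lists both the online self-report form and remote clinician review as core elements.

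**How the survey is routed** (Supplementary material, REDCap survey table):
- Question 6 asks whether the participant plans to adjust the weekly dose. On No, the "survey skips to question 20".
- Question 11 is the gateway to the symptom items: "Since your last INR, which of the following changes have occurred". It offers bleeding, clotting, illness, medication and diet categories, each opening one follow-up (questions 12 to 16). On None, the "survey skips to question 18".
- Question 17 asks: "Did you contact your anticoagulation management service provider regarding these symptoms". It has Yes and No as responses and no listed action.
- Question 21 is a "Text box for patient comments".

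**The contact rule.** *Participant clinical decision support tools* states: "Participants will be instructed to contact their anticoagulation clinician in high-risk situations (e.g., INR <1.5 or >5.0, any bleeding or thromboembolic symptoms", and also names scheduled invasive procedures. For the self-management phase the rule is repeated: "Participants will be asked to contact clinicians in high-risk situations as previously described or when additional advice is desired". In the printed survey the only contact instruction is at question 5: "If INR is 5.0 or higher, patient instructed to contact their anticoagulation provider".

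**The concern.** Whether a participant plans to change the dose does not tell us whether they have bled or clotted. A participant with an in-range INR and blood in the urine may well keep the same dose. As printed, the form asks that participant nothing about symptoms.

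What is at stake is timely safety review. The site can act only on what the form records, and these participants dose independently for six months. The gap does not close at the next test, because question 11 looks back only to the previous INR. Symptoms in an interval that ends in a no-change INR fall outside the look-back of the following survey.

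A lesser matter is that the form prompts contact for high INR but prints no such prompt for INR below 1.5 or for symptoms, although the protocol body lists them together.

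**Working it through.** The protocol states no figure to reproduce. The check follows the printed routing of all 21 items and counts.

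**Current path after No at question 6**
- Answered: questions 1 to 6 (6 items) plus questions 20 and 21 (2 items) = 8.
- Bypassed: questions 7 to 19 = 19 − 7 + 1 = 13. Check: 8 + 13 = 21.
- Of the 8 answered items, none asks about symptoms. Question 21 is free text and could carry them only if the participant volunteers them.

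**Path if No at question 6 is routed through questions 11 to 17, then 20**

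Let k be the number of categories selected at question 11, from 0 (None) to 5 (bleeding, clotting, illness, medication, diet). Assume, as the printed routing implies, that only None skips ahead, so question 17 follows any other answer. On this branch None goes to question 20.
- k = 0: question 11 only, so 1 added item; total 8 + 1 = 9.
- k ≥ 1: question 11, k follow-ups and question 17, so k + 2 added items; total 8 + k + 2.

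| Selected at question 11 | Added items | Total answered |
|---|---|---|
| None | 1 | 9 |
| One category | 1 + 1 + 1 = 3 | 11 |
| Two categories | 1 + 2 + 1 = 4 | 12 |
| All five | 1 + 5 + 1 = 7 | 15 |

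The longest path on this branch is still 21 − 15 = 6 items short of the full list.

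**Contact instructions against the contact rule**

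| Trigger in the protocol body | Recorded where | Printed contact instruction |
|---|---|---|
| INR above 5.0 | Question 5 | Yes (from 5.0 upward, so slightly more cautious) |
| INR below 1.5 | Question 5 | None |
| Bleeding or thromboembolic symptoms | Questions 11 to 13 | None; question 17 only asks whether contact was made |

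One of these three recordable triggers has a printed instruction. The count depends on grouping: with bleeding and clotting taken separately it is one of four. The two gaps differ in weight. Question 5 precedes the skip, so an INR below 1.5 is always recorded and reaches site review. Symptoms are recorded only if question 6 was answered Yes.

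**The case against.** **The table is an outline.** A blank comment cell does not prove that the live form shows nothing. This stands for the missing prompts. It has less force for the skip, which is printed as an explicit rule and not inferred from silence.

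**Other safeguards exist.** Participants are told the contact rule outside the survey, and sites review the emailed summaries. The first stands. The second helps only with what is recorded, which on the No path excludes symptoms unless they are typed in.

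**Events are confirmed by EHR review.** The *Effectiveness* section says so, and it protects outcome ascertainment. Table 3, however, schedules the event chart reviews pre-study and post-study, which is too late to help someone bleeding in the second month.

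**Extra prompts are a preference.** This largely stands. Using the survey to prompt contact for high INR does not oblige the sponsor to do so for every trigger, and question 17 is itself a mild reminder on the full path.

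**Readings to resist.** A reader might infer that the survey contradicts the contact rule, or that participants go uninstructed at INR below 1.5 or with symptoms. The protocol does not support this: no section makes the survey the channel for that rule. Nor does it follow that bleeding or thromboembolic outcomes are lost, given the EHR review.

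**Conclusion.** The routing at question 6 works against the form's stated purpose. Followed as printed, it removes 13 of 21 items, including all symptom items, from every survey in which no dose change is planned. It leaves a free-text box as the only way for symptoms to reach the site through the form. The missing contact prompts are a secondary point.

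This is a minor safety improvement that could be made cheaply, not a statistical error. It rests on the printed table matching the live form. The protocol gives no rate of no-change INRs, low INRs or symptoms, so no number of affected patients is claimed. The primary outcome is unaffected: successful transition is defined by completing six months of self-management and does not draw on the symptom items.

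**What to change.** **Main change.** Route No at question 6 through questions 11 to 17 before question 20. On that branch, None at question 11 should lead to question 20, not question 18.

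**Optional.** Extend the question 5 contact instruction to INR below 1.5, and show one when bleeding or clotting symptoms are selected at question 11. Do not trigger it on No at question 17 alone. As printed, that item follows any answer other than None, so it would also fire for a diet or medication change by itself, which the contact rule's examples do not include.

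**Cost.**
- Enrollment began on March 1, 2023, so this is an edit to a live REDCap form, with IRB notification.
- Participants who plan no dose change answer 1 to 7 more items, as tabulated above.
- A few more clinic contacts are likely. Each may lower the share of INRs counted as independently managed under *Implementation (Fidelity)*; the protocol gives no basis for sizing this.
- Self-reported symptom counts before and after the edit will not be comparable, so record its date.

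If the live form already does this, correcting the supplement is enough. If follow-up is nearly complete, make the change in any survey version released with the toolkit, elements of which the Abstract says will be made public.

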#### **Discussion**

This study is designed to answer an important question regarding the feasibility of warfarin PSM implementation in the US healthcare system. While PSM is recommended as the preferred warfarin management strategy by evidence-based guidelines it is virtually unused in the US healthcare system despite being widely used elsewhere in the world. Our study team members previously identified addressable barriers to and potential facilitators of wider PSM

implementation from the perspective of US patients receiving warfarin and clinicians who manage them. The results of these earlier qualitative studies were used in the rationale and design of the protocol for this implementation study. Our study is intended to demonstrate the feasibility of PSM implementation in the US healthcare system and generate an implementation toolkit for use by others interested in exploring PSM use at their clinical sites.

This study will be among the largest to assess the feasibility of PSM implementation in US settings and the first to use an implementation toolkit specifically designed to address barriers and incorporate facilitators previously identified through qualitative focus groups and interviews with US clinicians and patients, respectively. To our knowledge only three small studies evaluating PSM in the US have been conducted to date. The planned enrollment of 150 patients for our study will exceed that of all previous US-based studies combined.

The proposed study will provide crucial information on the characteristics of patients likely to be interested in attempting PSM, the performance of PSM patient educational tools, the usability of clinical decision support tools, the capability of US patients to safely engage in PSM, and the acceptability of PSM workflows in US healthcare settings.

We chose the RE-AIM framework as it has been shown to highlight essential program elements including external validity that can improve the sustainable adoption and implementation of effective, generalizable, evidence-based interventions like PSM. Further, we chose to utilize anticoagulation management services that have achieved Anticoagulation Centers of Excellence status as defined by the Anticoagulation Forum based on the premise that successful PSM implementation at these sites will promote dissemination of PSM implementation strategies to other centers throughout the US.

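### The per-INR survey has no DIY option, merges caregivers with clinicians and skips no-change INRs, so it does not record dosing method as the protocol states and cannot alone supply the independent-management percentage

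*Protocol*

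**What the plan says.** **Tools and decision-makers.** The protocol's *Participant clinical decision support tools* section gives the toolkit two formal tools, an "online dosing tool ('My Warfarin') and a manual dosing method ('DIY dosing". It adds a third route: "Participants or their caregivers will also be allowed to make warfarin dosing decisions based on their own" experience. *Patient selection criteria* accepts a patient who relies on a willing and capable caregiver.

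**What is to be recorded.** *PSM implementation phase* says the REDCap form collects "the method used to arrive at dosing decision (i.e., My Warfarin, DIY, or using their own judgement". The end-of-phase survey in the same section asks which tools were used, if any.

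**What the form asks (Supplementary material).**
- Question 6 asks whether the weekly dose will change. *No* leads straight to question 20, the date of the next INR.
- Question 7, on who decided the new dose, offers "I did -Someone else/healthcare provider -Other". Its routing note reads: "If 'I did', question 8 is asked; otherwise, survey skips to question 9".
- Question 8, on how the dose was decided, offers "My warfarin website tool -My own decision -Other".
- Question 17 asks about contact with the anticoagulation service, but only about symptoms or changes just reported. Answering *None* at question 11 bypasses it.

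**What the data feed.** *Implementation (Fidelity)* plans the percentage of INRs that the participant managed independently and appropriately. It is defined by no contact with a clinician and no action that clinicians judged inappropriate. The *Discussion* lists "the usability of clinical decision support tools" among the information the study will provide.

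**The concern.** The text names three dosing methods and the form has a code for two of them. A DIY user must choose between the own-decision answer, which also holds unsupported judgement, and *Other*. One of the toolkit's two formal tools therefore cannot be linked to an individual INR, dose change or later INR control.

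The decision-maker item has a similar fault. A dose chosen by a caregiver, which the protocol allows within PSM, can carry the same code as a dose chosen by a clinician, which is what PSM is meant to replace.

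The skip after question 6 then removes decision-maker, method and contact for every INR without a dose change, although the fidelity percentage is to be assessed INR by INR. If the survey is its source, the numerator cannot be formed for those INRs, and caregiver-supported participants may be misclassified.

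**Working it through.** There is no planned figure to reproduce. The check compares the stated categories with the form and then follows each route through it.

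**Categories.** Promised in *PSM implementation phase*: My Warfarin, DIY, own judgement (3). Identified by question 8: My Warfarin and own decision (2), plus *Other*. Because DIY users may tick own decision, that second category is not clean either.

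**Routes.**

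| Route | Decision-maker | Method | Clinician contact |
|---|---|---|---|
| Q6 *No*, go to Q20 | not asked | not asked | not asked |
| Q6 *Yes*, Q7 *I did*, Q8 My Warfarin | participant | My Warfarin | only if a change is reported at Q11 |
| Q6 *Yes*, Q7 *I did*, Q8 own decision or *Other* | participant | DIY or judgement, not separable | as above |
| Q6 *Yes*, Q7 merged answer or *Other* | caregiver, clinician or other, not separable | not asked | as above |

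Only the second route gives both a decision-maker and an unambiguous method. No route asks about clinician contact in general: question 17 covers contact about reported symptoms or changes only.

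**Scale.** Assume 26 weeks in 6 months, testing every 1 to 2 weeks, one survey per INR, and all 150 participants completing:
- per participant: 26 / 2 = 13 to 26 / 1 = 26 surveys;
- in total: 13 × 150 = 1,950 to 26 × 150 = 3,900 surveys (N).

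This is the count of all surveys, not of affected ones. Let c be the share of INRs with a dose change, s the share of those answered *I did*, and m the share of those answered own decision or *Other* at question 8. Then:
- DIY not separable: N × c × s × m;
- decision-maker not separable and no method: N × c × (1 − s);
- none of the three items asked: N × (1 − c).

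The protocol gives none of c, s or m. Each can lie anywhere from 0 to 1, so no count can be stated. The first two groups cannot exceed N × c, the dose-change INRs.

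**Direction of error, only if question 7 is the classifier.** Reading the merged answer as clinician counts caregiver decisions as not independent, so the percentage is too low. Reading it as caregiver counts clinician decisions as independent, so it is too high.

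**The case against.** A reader might infer that the trial cannot report decision-tool use or independent management at all. The documents do not support that, for these reasons:

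- **Tool use.** My Warfarin is identified whenever the participant decides a dose change, and it is the only tool with a named adherence outcome. The final survey gives tool use per participant. No outcome under *Reach* to *Maintenance* asks for DIY use by INR, and the *Discussion* remark on usability sets no INR-level endpoint.
- **Independent management.** The definition rests on clinician contact and clinician judgement and does not mention question 7. Sites receive survey summaries (*Approaches for documenting PSM activities in the EHR*) and track PSM performance on case-report forms (*Inclusion and exclusion criteria*). A bias in this outcome is therefore conditional on the survey being its source.
- **Size.** It would be wrong to take 1,950 to 3,900 as the number affected by questions 7 and 8, since only dose-change INRs reach them. A caregiver might also tick *I did*; the form gives no instruction.

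These limits stand. They do not remove the mismatch. The final survey is given per participant at the end of the phase, so it does not deliver the per-INR method record that the text describes. The site summaries carry the form's own codes. The protocol names no other source for the independence percentage.

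**Conclusion.** The point holds as an inconsistency in data capture. Question 8 lacks a category that the protocol says is recorded. Question 7 does not separate caregivers from healthcare providers and, for anything but *I did*, records no method. Questions 6, 7 and 17 do not by themselves supply the data for the independent-management percentage.

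Whether that percentage is actually distorted depends on the unnamed data source, so no bias can be asserted outright. The affected share is unknown.

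The primary outcome, completion of 6 months of PSM (*Reach*), does not depend on questions 7 or 8. INR control and clinical events do not depend on them either. The form should be corrected because the edit is small and the lost data cannot be recovered afterwards.

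**What to change.** 1. **Question 8:** add the DIY dosing method as its own option.
2. **Question 7:** replace the merged answer with separate caregiver and healthcare-provider options, and ask question 8 after *I did* or the caregiver answer.
3. **Every INR:** ask decision-maker and clinician contact whatever the answer to question 6. Otherwise, name in *Implementation (Fidelity)* the other source of these data, for example the site case-report forms. Splitting question 7 alone leaves no-change INRs uncovered.
4. **Outcome definition:** state that caregiver decisions count as PSM in the independence percentage.
5. **Records collected before the edit** (enrollment began March 1, 2023): earlier DIY or caregiver decisions cannot be singled out. Report own decision and *Other* at question 8, and the merged answer and *Other* at question 7, as whole unclassified categories.

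The cost is a REDCap edit at all sites, a slightly longer survey, and earlier records that stay unclassifiable. No treatment rule changes.
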